# Efficacy of chloroquine versus lopinavir/ritonavir in mild/general COVID-19 infection: a prospective, open-label, multicenter, randomized controlled clinical study

**DOI:** 10.1186/s13063-020-04478-w

**Published:** 2020-07-08

**Keywords:** COVID-19, Chloroquine, Lopinavir/ritonavir, Randomized controlled clinical study, Efficacy

## Abstract

**Background:**

The outbreak of COVID-19 (caused by SARS-Cov-2) is very serious, and no effective antiviral treatment has yet been confirmed. The adage “old drug, new trick” in this context may suggest the important therapeutic potential of existing drugs. We found that the lopinavir/ritonavir treatment recommended in the fifth edition of the Treatment Plan of China can only help to improve a minority of throat-swab nucleic-acid results (3/15) in hospitals. Our previous use of chloroquine to treat patients with COVID-19 infection showed an improvement in more throat-swab nucleic-acid results (5/10) than the use of lopinavir/ritonavir.

**Methods/design:**

This is a prospective, open-label, randomized controlled, multicenter clinical study. The study consists of three phases: a screening period, a treatment period of no more than 10 days, and a follow-up period for each participant. Participants with COVID-19 infection who are eligible for selection for the study will be randomly allocated to the trial group or the control group. The control group will be given lopinavir/ritonavir treatment for no more than 10 days. The trial group will be given chloroquine phosphate treatment for no more than 10 days. The primary outcome is the clinical recovery time at no more than 28 days after the completion of therapy and follow-up. The secondary outcomes include the rate of treatment success after the completion of therapy and follow-up, the time of treatment success after no more than 28 days, the rate of serious adverse events during the completion of therapy and follow-up, and the time to return to normal temperature (calculated from the onset of illness) during the completion of therapy and follow-up. Comparisons will be performed using two-sided tests with a statistical significance level of 5%.

**Discussion:**

This experiment should reveal the efficacy and safety of using chloroquine versus lopinavir/ritonavir for patients with mild/general COVID-19 infection. If the new treatment including chloroquine shows a higher rate of throat-swab SARS-CoV-2 real-time fluorescent reverse transcription polymerase chain reaction (RT-PCR) negativity and is safe, it could be tested as a future COVID-19 treatment.

**Trial registration:**

Chinese Clinical Trial Registry, ID: ChiCTR2000029741. Registered on 11 February 2020.

## Introduction

### Background

In December 2019, patients with unexplained pneumonia appeared in Wuhan, China, and were subsequently identified as a having a novel type of coronavirus. On 30 January 2020, the World Health Organization named it “COVID-19 (Corona Virus Disease-2019, caused by Severe Acute Respiratory Syndrome Corona Virus (SARS-Cov-2)).” The COVID-19 epidemic is now spreading throughout the world.

Coronavirus is a single-stranded, positive-strand RNA (ribonucleic acid) virus with an envelope [1]. There are currently no clinically specific drugs for HCoVs (Human Corona Viruses). Recently, the National Health Commission of China announced a new coronavirus-infection-related pneumonia diagnosis and treatment program (the fifth edition, URL: http://www.nhc.gov.cn/yzygj/s7653p/202002/3b09b894ac9b4204a79db5b8912d4440/files/7260301a393845fc87fcf6dd52965ecb.pdf), which proposed the trial of lopinavir/ritonavir for its antivirus effect [2–4]. Our previous use of this drug combination found that the effect of lopinavir/ritonavir on COVID-19 was unsatisfactory, as it only helps to improve the minority of throat-swab nucleic-acid results (3/15).

Chloroquine is not only used as an antimalarial drug, but is also used for the treatment of autoimmune diseases due to its immunomodulatory activity [5].

Previous studies have shown that chloroquine exerts antiviral effects through the following mechanisms:
It can change the pH of acidic organelles [6] (such as endosomes), so inhibits infections such as Borna disease virus [7], avian leukemia virus [8], and Zika virus [9]It can change the glycosylation pattern of the HIV virus gp120 envelope, which inhibits the replication of HIV (human immunodeficiency virus) virus in CD4 + T cells [10]It can effectively inhibit autophagy in the lungs of avian influenza H5N1 mice and reduce the damage to the alveolar epithelium [11]It inhibits viral replication by blocking the autophagy phenomenon induced by the Zika virus, and can cut off vertical infection of the Zika virus from the maternal-fetal pathway [12]

Multiple studies have found that chloroquine has anti-SARS-CoV activity:
Chloroquine can inhibit viral replication by reducing the terminal glycosylation of the angiotensin-converting enzyme 2 (ACE2) receptor on Vero E6 cells and interfering with the binding of SARS-CoV to the ACE2 receptor [13, 14]Chloroquine inhibits the replication of HCoV-229E (and SARS-CoV, both belong to the α-group HCoVs) by inhibiting the activation of p38 mitogen-activated protein kinase (MAPK) in the L132 human embryonic-lung-cell line [15]The spike protein (S protein) of SARS-CoV-2 is similar in structure to that of SARS-CoV, and can bind to the ACE2 receptor on the host-cell surface to infect the host epithelial cells [16]Remdesivir (GS-5734) and chloroquine (Sigma-C6628) can effectively inhibit SARS-CoV-2 infection [17]

This study will compare the efficacy, safety, and impact on patient compliance between the chloroquine phosphate regimen with the lopinavir/ritonavir regimen in mild/general COVID-19 infection.

## Methods/design

### Setting

This randomized controlled trial is to be conducted at the Fifth Affiliated Hospital of Sun Yat-sen University, the Ninth People’s Hospital of Dongguan, Zhongshan Second People’s Hospital, and Jiangmen Central Hospital.

These hospitals are located in Guangdong, China. The clinical research flowchart (CRF) of the research process is shown in Fig. 1.

**Fig. 1 Fig1:**
[figure not shown]
The clinical research flowchart

Once the volunteered participants have been included, researchers will explain the research procedures in detail and require them to sign a written informed consent form which is signed by the subjects or their legal representative. All participants can withdraw their consent at any time during the trial.

### Design

This is a prospective, open-label, randomized controlled, multicenter clinical study with two arms. Eligible patients are first screened by safety laboratory testing. Patients with diagnosed mild/general COVID-19 infection are randomized to the following two arms at a 1:1 ratio:
Arm 1 (control arm): lopinavir/ritonavir treatment for diagnosed mild/general COVID-19 infection uses lopinavir 800 mg/day and ritonavir 200 mg/day for no more than 10 daysArm 2 (investigation arm): chloroquine phosphate treatment using chloroquine phosphate 1000 mg/day, equivalent to chloroquine 600 mg/day for no more than 10 days

The CRF is shown in Fig. 1. The schedule of treatment visits and data collection (also known as the CRF) is shown in Table 1.

**Table 1 Tab1:**
[figure not shown]
The schedule of treatments and data collection

The *SOFA (Sequential Organ Failure Assessment) score* predicts mortality risk for patients in the intensive care unit based on laboratory results and clinical data^1^

*Coagulation index*: *PT* prothrombin time, *APTT* activated partial prothrombin time, Fib fibrinogen, *D-Dimer* D-dimer, *PLT* platelet count

*Inflammatory factors*: various cytokines involved in inflammation, such as interleukin (IL)-6, IL-10, tumor necrosis factor (TNF)-α, etc.

*PCT (procalcitonin)*: a protein that increases when severe bacterial, fungal, and parasitic infections, sepsis, and multiple organ failure occur

− D0: before the research; D0: start of the research; D1: 1st day of the research; D2: 2nd day of the research; D3: 3rd day of the research; D4: 4th day of the research; D5: 5th day of the research; D6: 6th day of the research; D7: 7th day of the research; D10: 10th day of the research; D14: 14th day of the research; D21: 21st day of the research; D28: 28th day of the research; D29: after the research

References:

1 Medlej K. Calculated decisions: sequential organ failure assessment (SOFA) score. *Emerg Med Pract* 2018;20:CD1-CD2.

Researchers will evaluate treatment adherence during each visit. If a scheduled visit is delayed or cancelled, the research team will contact the participant at once. No treatment or intervention is prohibited for any of the participants.

### Outcomes

The primary outcome is the clinical recovery time of no more than 28 days after the completion of therapy and follow-up. The secondary outcomes include the rate of treatment success after the completion of therapy and follow-up, the time of treatment success after no more than 28 days, the rate of serious adverse events (SAEs) during the completion of therapy and follow-up, and the time to return to normal temperature (calculated from the onset of illness) during the completion of therapy and follow-up.

### Definitions

#### The clinical recovery time and adverse events

We define the clinical recovery time as the time (in hours, no more than 28 days) from the start of study drug intervention to normalization of body temperature, respiratory symptoms (cough, nasal stuffiness, nasal discharge, etc.), respiratory frequency, and blood-oxygen saturation. Specifically, also meeting the following criteria at the same time:
① No fever: axillary body temperature ≤ 37.2 °C② Relief of respiratory symptoms (72 consecutive hours)③ Respiration rate ≤ 24/min (resting state)④ Fingertip blood oxygen > 94%

Adverse events (AEs) refer to adverse medical events that occur after a patient or clinical trial participant receives a drug, but they are not necessarily causally related to treatment.

Serious adverse events (SAEs) refer to events that require hospitalization, prolonged hospital stay, disability, affect working ability, are life-threatening or fatal, cause congenital malformation and other events that occur during the clinical trial.

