### Randomization

Grouping is carried out using a centrally stratified, randomized block method. Before the trial, a statistical expert will use SAS software to set the number of centers at four, the block size will be four, the number of blocks will be 28, using a 1: 1 ratio between the experimental group and the control group, will generate 112 random numbers and corresponding grouping information. According to the haphazard allocation table used in advance, the statistical expert gives random numbers (1–112) in ascending order. Each random number and grouping information correspond to an envelope. The envelope is sealed and given to the researchers responsible for screening. Qualified subjects are selected, and the envelopes are received in the order of enrollment. After the envelopes are opened, the random-number and grouping information is removed, so that the subjects will be randomly assigned to the experimental group or the control group, and the corresponding treatment and observations performed. Each subject’s random number is unique and remains the same throughout the trial.

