### Sample size

The hypothesis of this study is that the use of chloroquine phosphate instead of lopinavir/ritonavir will increase the rate of throat-swab SARS-CoV-2 nucleic-acid negative conversion.

The main therapeutic index of this study is the clinical recovery time (after no more than 28 days), which is from the beginning of the study drug intervention treatment to the normalization of body temperature, respiratory symptoms, respiratory rate, and blood-oxygen saturation. In the later analysis, the log-rank method is used to compare the differences in clinical recovery time between the two groups of patients. The sample size of this study is calculated based on the log-rank method by using the log-rank test (Lakatos) (median survival time) module in the PASS 11.0 statistical software (see Additional file: Sample size report” for details).

Based on clinical experience [4, 18], the median clinical recovery time of the patients in the control group is expected to be 8 days, and the median clinical recovery time of patients in the experimental group can be shortened to 4 days (corresponding hazard ratio (HR) = 2.0) 112 patients (56 in each group) will be required to detect this difference with a significant level of *α* = 0.05 (both sides) with 85% confidence interval.

The trial is planned to be enrolled for 90 days, followed up for 28 days, and a final analysis is performed after 78 clinical recovery events occur. It is estimated that the drop-out rate of the experimental group and the control group is 5%.

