### Statistical analysis

The results of this study for efficacy outcomes will be analyzed based on both intention-to-treat (ITT) and per-protocol (PP) approaches with a primary consideration for ITT results. A PP analysis will be performed secondarily. A safety analysis will be performed based on the safety group.

The ITT group will include participants who are randomized after satisfying the eligibility criteria and receive one study drug at least once and have post-dose evaluation data. The PP group will include participants who satisfy the following conditions among the ITT group: (1) those who completed all planned visits and (2) those who did not receive and use drugs or treatments that may affect the evaluation of efficacy during the study. The safety analysis group will include participants who received study drugs at least once and have post-dose safety evaluation data.

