### Efficacy outcomes

Comparisons will be performed using two-sided tests with a statistical significance level of 5% unless stated otherwise.

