#### Analysis of primary outcomes

For the primary outcome of this trial, the clinical recovery time of no more than 28 days after the completion of therapy and follow-up will be estimated as the proportion with a 95% confidence interval (CI) for each treatment group. The difference between the control arm and the experimental arm will subsequently be determined using the log-rank test. In order to control the influence of possible confounding factors such as gender and age on the clinical recovery time, the Cox proportional hazard model will be used to compare whether the clinical recovery time of the two groups is different, provide HRs and 95% CIs.

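### The primary recovery clock starts at first study drug, not at randomisation, which leaves an open-label comparison exposed if time to first dose differs between arms

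*Protocol article*

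**What the plan says.** The definition of clinical recovery time in the protocol article (section The clinical recovery time and adverse events) runs "from the start of study drug intervention to normalization of body temperature" and of respiratory symptoms, respiratory rate and oxygen saturation. It is measured in hours up to 28 days. The Sample size section repeats the origin: "which is from the beginning of the study drug intervention treatment to the normalization of body temperature". The starting point is therefore fixed twice and is not left to a later document.

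The Design section describes the trial as follows: "This is a prospective, open-label, randomized controlled, multicenter clinical study with two arms". Patients are "randomized to the following two arms at a 1:1 ratio". Under Randomization, sealed envelopes are used in order of enrolment: "After the envelopes are opened, the random-number and grouping information is removed", and treatment follows. The text sets no limit on the interval between opening the envelope and the first dose, and it does not say that the two fall on the same day.

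The Statistical analysis section gives primary consideration to a set called ITT. To be in it, a randomised patient must also "receive one study drug at least once and have post-dose evaluation data". The primary test is named under Analysis of primary outcomes: "The difference between the control arm and the experimental arm will subsequently be determined using the log-rank test". A Cox model adjusting for factors such as gender and age follows.

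**The concern.** Randomisation makes the arms comparable at the moment of randomisation. First dose comes later and is reached with the arm known to patient and clinician. If one arm tends to be dosed later, its clock starts later in a self-limiting illness, and the part of the course already lived through is discarded.

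The sample-size assumptions are medians of 4 and 8 days and the endpoint is recorded in hours, so a difference of half a day or a day is not small on this scale. Patients who recover or withdraw before dosing are a second route. They are either scored at almost no time or dropped by the dosing condition of the analysis set. Adjusting the Cox model for gender and age repairs neither. At stake is the false-positive rate of the primary test and an apparent hazard ratio above 1 that no drug effect has produced.

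**Working it through.** **The plan's own figures.** Inputs from the Sample size section are medians of 8 and 4 days, HR 2.0, two-sided alpha 0.05, 85% (taken as power), 90 days of enrolment, 28 days of follow-up and 5% drop-out.

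- Schoenfeld events: 4 × (1.960 + 1.036)² / (ln 2)² ≈ 75.
- Freedman events: (1.960 + 1.036)² × (2 + 1)² / (2 − 1)² ≈ 81.
- Lakatos log-rank calculation with 5% drop-out per day: N ≈ 110. At N = 112, power is about 85.6% and about 78 events are expected.

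The stated 112 patients and 78 events are thus reproduced if the drop-out is a daily rate. With 5% over the whole study or the follow-up, N would be about 81. Nothing below disputes these figures, and moving the time origin alters none of their inputs.

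**Does a delay bias the test?** Let recovery time from randomisation have survival S(t), the same in both arms (no drug effect), and let one arm be dosed d days later. Among its patients not yet recovered at first dose, survival on the first-dose clock is S(t + d)/S(d).

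- Constant hazard: exp(−λ(t + d))/exp(−λd) = exp(−λt), so there is no bias.
- Weibull shape k: the hazard ratio of the delayed to the undelayed arm is ((t + d)/t)^(k−1). With k = 2 and d = 1 this is 5/4 = 1.25 at day 4 and 9/8 = 1.125 at day 8. For k > 1 it favours the later-dosed arm. For k < 1 it would go the other way.

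**Pre-dose recoveries.** With median 8 days, the share recovered by day 1 is 1 − 2^(−(1/8)^k).

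- k = 1: 8.3%, or 4.6 of 56.
- k = 1.5: 3.0%, or 1.7 of 56.
- k = 2: 1.1%, or 0.6 of 56.

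How they are scored therefore matters most under a constant hazard.

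**Simulation.** Settings: 56 per arm, both medians 8 days from randomisation, censoring at 28 days, two-sided 5% log-rank test, 10,000 null trials per first-dose setting (simulation error about ±0.4 points at 5%). The delay and the Weibull shapes are assumptions. The table shows an arm difference of one day.

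| Weibull shape | Pre-dose recoveries left out: error (HR) | Kept at time zero: error (HR) | Randomisation clock: error |
|---|---|---|---|
| 1 (constant) | about 5% (1.00) | about 8% (1.10) | 5–6% |
| 1.5 | about 9% (1.11) | about 11% (1.15) | 5–6% |
| 2 | about 16% (1.21) | about 17% (1.21) | 5–6% |

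- A half-day difference gives about 5 to 8%: near nominal at shape 1, up to about 7% at shape 1.5, about 8% at shape 2.
- A two-day difference with pre-dose recoveries left out gives about 5%, 17% and 43% for shapes 1, 1.5 and 2 (HR 1.00, 1.22 and 1.43).
- With no arm difference in delay, the error is nominal.

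**The case against.** The strongest reply is that the text shows no harm. Nothing in it gives or suggests an arm difference in time to first dose. The Randomization section runs envelope opening, assignment and treatment together as one sequence. The legend to Table 1 names a single day zero, and the grid, which might settle the timing, is not available here. Both treatments are existing drugs that the investigators had already used. All of this stands. It limits the point to a risk, and a reader who infers that this trial's result is biased goes beyond the documents.

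A reader might also infer that any arm difference in delay distorts the comparison. That is too strong. Under a constant recovery hazard, which is the reading that turns medians of 8 and 4 days into HR 2.0, a delay alone leaves the log-rank test at its nominal level once pre-dose recoveries are left out. The inflation to about 8% in that case comes only from keeping them at time zero. That scoring is itself an assumption. The definition asks for 72 consecutive hours of symptom relief and does not say whether recovery is dated at the start or the end of that window.

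Finally, the dosing condition in the analysis set is a distinct feature, and moving the clock alone would not bring undosed patients back. This is right, and the fix has to cover both.

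The rule itself remains. The origin is stated twice as first dose, and nothing in the text ties first dose to randomisation.

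**Conclusion.** The point holds as a low-severity weakness in a stated rule. The primary clock starts at an event after randomisation, reached with the arm known. Bias arises only if time to first dose differs between arms and, in addition, the recovery hazard changes over time or pre-dose recoveries are scored near zero. With a rising hazard it favours the later-dosed arm.

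The size rests wholly on assumptions about delay and hazard shape. It runs from nothing (equal delays) to the 15 to 17% error in the most affected one-day setting tabulated. A larger delay difference would do more harm. Same-day dosing in both arms would make the matter negligible.

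It should also not be inferred that a randomisation clock removes the effect of a delay on outcome. It counts the delay as part of the assigned strategy and keeps the randomised comparison intact.

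**What to change.** 1. In the definition of clinical recovery time and again in the Sample size section, count the time from randomisation (the opening of the envelope), and run the 28-day limit from the same point.
2. Apply this to all randomised patients in the primary analysis, without requiring a dose or post-dose data. Patients who recover before dosing then count with their actual time, and those who withdraw are censored when last observed.
3. Keep time from first dose as a sensitivity analysis, and report the interval from envelope opening to first dose by arm so that readers can see whether the issue arose.

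The cost is small. The envelope-opening time must be recorded, or recovered for patients already enrolled, since recruitment was still under way at publication. Recovery must also be followed in patients who are not dosed. Measured times become slightly longer in both arms. The 112 patients and 78 events stay as they are.

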### Participants

#### Inclusion criteria

Age ≥ 18 yearsPatients diagnosed with COVID-19 according to the criteria of the seventh edition of the Treatment Plan of China for new coronavirus pneumonia (URL: http://202.116.81.74/cache/4/03/www.nhc.gov.cn/5d9aa1423a8a577e1cc197a0d3c434d8/ce3e6945832a438eaae415350a8ce964.pdf):
① Epidemiological history:
Within 14 days before the onset of illness, a history of travel or residence in Wuhan and surrounding areas, or other communities with reported casesWithin 14 days before the onset of illness, exposure to a person with COVID-19 infection (positive nucleic-acid test)Exposure to patients with fever or respiratory symptoms from Wuhan and surrounding areas, or communities with case reports within 14 days before illness onsetAggregated disease: two or more cases of fever or respiratory symptoms occurring in a small area, such as home, office, school class, etc., within 2 weeks② Clinical manifestations:
Fever or respiratory-tract symptoms: cough, nasal stuffiness, nasal discharge, etc.Normal or decreased white-blood-cell counts in the early stages of disease; normal or decreased lymphocyte countsMultiple, small, patchy shadows and interstitial changes in the early stages of chest imaging, which are evident in the extrapulmonary zones, and which develop multiple “ground-glass” infiltrations and infiltrates throughout both lungs. In severe cases, pulmonary consolidation may occur, but the formation of pleural effusion is rare③ Confirmed conditions: fulfillment of any one of the epidemiological history items and any two of the clinical manifestation items or three clinical manifestation items if no epidemiological history is available, in addition to meeting one of the following etiological or serological criteria:
Real-time fluorescent RT-PCR detects novel coronavirus nucleic acidThe gene-sequencing results of patients’ specimens (blood, stool, etc.) are highly homologous to those of known novel coronavirusesSerum SARS-CoV-2-specific antibodies IgM and IgG are positive, serum SARS-CoV-2-specific IgG antibodies change from negative to positive or the quantity of IgG in the recovery phase is at least four times higher than in the acute phase (3–5 days after illness onset)Mild or general patients:

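### The 72-hour condition in the primary endpoint covers respiratory symptoms only, so as written one in-range temperature reading can complete an irreversible recovery event

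*Protocol article*

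**What the plan says.** In the Protocol article, under the definition of clinical recovery time, the primary outcome is a time in hours with a 28-day cap, running "from the start of study drug intervention to normalization of body temperature, respiratory symptoms (cough, nasal stuffiness, nasal discharge, etc.), respiratory frequency, and blood-oxygen saturation". The text then makes this operational: "Specifically, also meeting the following criteria at the same time". The four criteria are:

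1. "No fever: axillary body temperature" at or below 37.2 °C.
2. "Relief of respiratory symptoms (72 consecutive hours", with the duration in parentheses after this item alone.
3. Respiratory rate of at most 24/min ("resting state").
4. "Fingertip blood oxygen > 94" percent.

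Under Inclusion criteria, one qualifying clinical item is "Fever or respiratory-tract symptoms: cough, nasal stuffiness, nasal discharge, etc", so fever without respiratory symptoms satisfies it. The same section describes mild disease by low-grade fever, slight fatigue and an open-ended et cetera, without pneumonia on imaging. The Design section states that the trial is open-label, and the text following Table 1 bars no concomitant treatment. Analysis of primary outcomes specifies a log-rank test and a Cox model.

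**The concern.** A time-to-event analysis takes the first qualifying moment as final. If a component can be met momentarily, a dip in an intermittent fever, or a dip produced by an antipyretic, is recorded as recovery and stays recorded when the fever returns. Only the symptom criterion guards against this. For a patient with no respiratory symptoms at entry, that guard may do little, and temperature can be the only abnormal component. The primary event is then nearly the same as the secondary outcome of time to normal temperature, apart from the time origin (start of drug rather than onset of illness).

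Two things are at stake: false recoveries inside the primary endpoint, and an endpoint whose persistence requirement differs between patients who are analysed together.

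**Working it through.** The plan gives no figure for reading frequency, fever pattern or the share of patients without respiratory symptoms. The check is therefore mainly textual. The figures under Sample size (medians of 8 and 4 days, hazard ratio 2.0, 78 events, 112 patients) do not enter it.

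**Step 1: duration attached to each component.**

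| Component | Threshold | Stated duration |
|---|---|---|
| Axillary temperature | ≤ 37.2 °C | none |
| Respiratory symptoms | relief | 72 consecutive hours |
| Respiratory rate | ≤ 24/min at rest | none |
| Oxygen saturation | > 94% | none |

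The phrase "also meeting the following criteria at the same time" requires that the four coincide. It does not say for how long. By contrast, the Treatment outcomes section does set a persistence rule for the virological secondary outcome: two negative swabs in a row that stay negative. The primary outcome has the weaker rule.

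**Step 2: two patients under the wording.**

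- *Respiratory symptoms at entry, now relieved for 72 hours, fever intermittent, rate and saturation in range.* Criteria 2, 3 and 4 hold. The first reading at or below 37.2 °C completes the event, whatever the next reading shows.
- *Fever but no respiratory symptoms at entry, rate and saturation in range.* Criteria 3 and 4 hold at baseline. Criterion 2 holds at baseline or, if its clock starts at the first dose, at 72 hours. In either case one qualifying reading is then enough.

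**Step 3: what a duration would change for one patient (illustration on assumed inputs).** Let a patient who is still in the febrile phase have probability *p* of an in-range reading, with one reading a day, independent readings, and the other three criteria already met. Four daily readings span 72 hours.

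- At least one in-range reading among four: 1 − (1 − p)⁴
- All four in range: p⁴

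| p (assumed) | single reading suffices | all four required |
|---|---|---|
| 0.1 | 1 − 0.6561 = 34% | 0.01% |
| 0.2 | 1 − 0.4096 = 59% | 0.16% |
| 0.3 | 1 − 0.2401 = 76% | 0.81% |

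Real readings are correlated, so the contrast would be smaller in practice. The table shows why persistence matters; it does not estimate anything for this trial.

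**Step 4: direction for the treatment comparison.** Suppose true recovery hazards are a (chloroquine) > b (control), and false events add the same hazard h > 0 in both arms. Then (a + h)/(b + h) lies between 1 and a/b. The pull is toward 1 on the condition of equal frequency, which the protocol neither states nor secures.

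**The case against.** The best reply is that silence is not a rule. The definition asks for normalization of all four components together. Since one of them is itself a 72-hour state, the investigators may have meant all four to hold over that period. Reading frequency and confirmation may also be set out in Table 1, which is not shown, or in a fuller protocol, and an endpoint in hours suggests readings more often than once a day. This stands to the extent that the intention may be sound. It does not remove the point: the article gives a full operational definition, puts the duration on one item of four, and lets two assessors date the same patient's recovery differently.

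Two stronger readings are tempting and are not supported.

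- *A reader might infer that mild patients as a class have only fever, so that the endpoint has no persistence for any of them.* The mild description is open-ended, and a mild patient may enter with respiratory symptoms. Normal rate and saturation are not stated for this class either. Only some mild patients fit the second case in the working, and for them a 72-hour clock from first dose would still bar events before 72 hours.
- *A reader might add a false-event hazard to the hazards implied by medians of 8 and 4 days and quote a diluted hazard ratio.* Those medians are stated for the endpoint as planned. Adding, say, 0.10 per day to the control hazard ln 2/8 = 0.087 gives a median of ln 2/0.187 = 3.7 days, which is not the plan's 8. The false-event rate, its equality between arms and the share of patients affected are all unknown. A treatment that lowers temperature may itself change how often in-range readings occur.

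**Conclusion.** The concern holds as a defect in the endpoint wording. The duration is attached to respiratory symptoms only, and a single in-range temperature can complete recovery once the other three criteria are met. The patients exposed are those with fluctuating fever whose respiratory symptoms have eased for 72 hours, and those who never had such symptoms. The protocol does not give their number.

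The pull of the hazard ratio toward 1 rests on equal frequency of false events in both arms. In an open-label trial with unrestricted concomitant treatment that is an assumption, and without it the direction is not fixed. No size for the effect on the hazard ratio, the medians or power can be derived from the document, and none is claimed. The change is worth making because the primary endpoint depends on it, but the defect does not make the trial unanalysable.

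**What to change.** Amend the definition of clinical recovery time so that the existing 72 hours applies to all four criteria jointly:

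- Recovery is dated to the start of the first 72-hour period in which every recorded temperature, respiratory rate and saturation is in range and respiratory symptoms are relieved.
- For a patient without respiratory symptoms at D0, the symptom criterion means that none appears during that period.
- A minimum number of recorded readings within the period is required, with the number set by the investigators. Otherwise a sparsely observed patient could still qualify on very few values.

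The text change is a few sentences. There are two costs. Recoveries that begin in the last 3 days before D28 cannot be confirmed. Also, the listed days after D7 are D10, D14, D21 and D28 (gaps of 3, 4, 7 and 7 days), so scheduled visits alone cannot document a continuous 72 hours and readings between visits are needed. The endpoint in hours and the present 72-hour symptom rule already presuppose such readings. Whether they are already collected cannot be confirmed while Table 1 is not shown.
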